# Effects of a brief, pedometer-based behavioral intervention for individuals with COPD during inpatient pulmonary rehabilitation on 6-week and 6-month objectively measured physical activity: study protocol for a randomized controlled trial

**DOI:** 10.1186/s13063-017-2124-z

**Published:** 2017-08-29

**Keywords:** Behavior-change intervention, Chronic obstructive pulmonary disease (COPD), Implicit association test, Pedometer, Accelerometry, Physical activity-related health competence, Health-related quality of life (HRQoL)

## Abstract

**Background:**

Pulmonary rehabilitation programs often fail to substantially enhance long-term physical activity in patients with chronic obstructive pulmonary disease (COPD). The reasons for successful physical activity changes in patients with COPD are not well understood. The need to better understand the determinants of physical activity in patients with COPD and effective rehabilitation strategies to improve physical activity is evident.

**Methods/design:**

The STAR study (Stay Active after Rehabilitation) investigates, in a randomized controlled trial, the additional effect of a pedometer-based behavior-change intervention during inpatient pulmonary rehabilitation on objectively measured physical activity 6 weeks and 6 months post rehabilitation. The intervention uses the behavior-change techniques (1) instruction on how, where and when to perform the behavior, (2) prompt goal setting for physical activity, (3) prompt self-monitoring of behavior, and (4) feedback on behavior. The primary outcome of physical activity will be measured using a physical activity monitor (Actigraph wGT3X-BT) for a period of 7 days, firstly 2 weeks before rehabilitation begins (t0) as well as 6 weeks and 6 months after rehabilitation (t3, t4). Additionally, to predict physical activity progression after rehabilitation, a complex personal diagnostics battery, including questionnaires as well as functional assessments, is to be carried out at the start and end of rehabilitation (t1, t2). This battery is based on the foundational ideas of the Physical Activity-Related health Competence model.

Five hundred and two patients with COPD, aged 18 years or older and admitted for an approved pulmonary rehabilitation, will be enrolled in the STAR study.

**Discussion:**

The STAR study is designed as a randomized controlled trial to gain a better understanding of the personal determinants of physical activity in patients with COPD and to evaluate a pedometer-based physical activity-change intervention in the context of inpatient pulmonary rehabilitation. The results enable the future identification of patients with COPD who will find it difficult to engage in long-term physical activity after rehabilitation. Based on this, intervention strategies to promote physical activity in the content of pulmonary rehabilitation can be optimized.

**Trial registration:**

Clinicaltrials.gov, ID: NCT02966561. Registered retrospectively after the start of the recruitment in June 2016 on 22 November 2016. All protocol modifications will be registered in the trial registry.

**Electronic supplementary material:**

The online version of this article (doi:10.1186/s13063-017-2124-z) contains supplementary material, which is available to authorized users.

## Background

The initiation of a physically active lifestyle is a central goal of pulmonary rehabilitation (PR) [1]; though in patients with chronic obstructive pulmonary disease (COPD), PR programs often fail to substantially enhance long-term physical activity (PA) [2–4]. The reasons for successful PA behavior changes in patients with COPD are not well understood [5]. The role of psychological factors especially, and their interplay with physical functioning needs further investigation [6]. Consequently, following Spruit et al. [4], two aspects are needed for optimized patient treatment during PR: (1) a better understanding of the determinants of PA in patients with COPD and (2) effective strategies to improve important determinants and, accordingly, PA.

In covering the first point, the concept of Physical Activity-related health Competence (the PARC model) provides a new model to describe personal determinants of PA [7]. The PARC model focuses on personal competencies that favor the integration of PA in everyday life. The model’s three components are movement competence, control competence, and self-regulation competence. These subcompetencies are directly linked to the requirements for initiating and maintaining PA with positive effects on health and wellbeing. In comparison to other health psychology models of health behavior, the competence-based perspective of the PARC model is considered to add value because it contains movement-related, task-specific as well as sport-typical elements. Notably, the PARC model incorporates important individual physical and psychological characteristics. This is especially important for the explanation of PA behavior of older adults and clinical populations. The first validated, generic questionnaire for the subcompetencies of the PARC model is now available [7]. For clinical populations, this questionnaire could profit from an extension with indication-specific characteristics (e.g., obstructive lung function for patients with COPD), allowing for a complex and adequate assessment of individual determinants of PA in clinical populations.

With regard to the second point, the use of pedometers ranks as one of the most effective intervention elements for PA promotion [8]. Pedometers offer various possibilities to design behavior-change strategies [9]. In particular, pedometers are of use for persons to monitor and record their daily PA. Self-monitoring of behavior has been proven to be one of the most effective behavior-change techniques (BCT) in clinical populations [10]. Furthermore, pedometers are suitable in support of other BCT [11], e.g., individual goal setting in the unit steps per day or giving feedback on behavior. In nonclinical populations, pedometer-based interventions achieve an average increased PA level of approximately 2000 steps per day (effect size *d* = 0.68) in comparison to control groups [12]. Clinical populations provide preliminary evidence for the effectiveness of pedometers as part of rehabilitation for people with musculoskeletal disease [13], type-2 diabetes [14] as well as COPD [15, 16]. However, these results come from studies with small sample sizes in outpatient rehabilitation programs. Moreover, these studies often relate to short-term behavior changes during the rehabilitation period. The validity of most studies is further restricted by the usage of PA questionnaires instead of objective PA measurements [4]. Singh et al. [17] summarized that pedometer studies’ sample sizes in PR were not, up to this point, suitable for the detection of meaningful differences in PA levels. In the context of inpatient PR the potential of pedometers to first initiate and afterward maintain a physically active lifestyle in the long term has not yet been investigated.

The purpose of this paper is to describe the design of a randomized controlled trial (RCT) to (1) evaluate the effect of a short, pedometer-based behavior-change intervention (BCI) for inpatient PR in COPD patients with regard to the initiation (6-week follow-up) and maintenance (6-month follow-up) of a physically active lifestyle after PR and (2) to predict the expected intervention treatment effect and PA progression after PR discharge utilizing an innovative diagnostic battery that is based on the PARC model [7].

The STAR study (Stay Active after Rehabilitation) aims to answer two central questions: does the integration of a pedometer-based intervention during inpatient PR for people with COPD, in comparison to standard PR, lead to a sustained improvement of PR results with regards to PA 6 weeks and 6 months after the PR? how does PA-related health competence of individuals with COPD develop during inpatient PR; and which individual PA-related health competence characteristics, in combination with which disease-specific prognostic assessments, enable the prediction of the expected intervention treatment effect as well as of the initiation and long-term maintenance of a physically active lifestyle after PR?

### Hypothesis

#### Primary hypothesis

In individuals with COPD, inpatient PR (= standard care) plus a pedometer-based BCI will result in a significantly higher level of PA 6 weeks and 6 months after rehabilitation compared to standard care plus a short revision of patient education.

#### Secondary hypothesis

The secondary outcomes (PA-related health competence of patients with COPD in combination with other PA behavior-related psychological measurements and disease-specific prognostic assessment) will enable the explanation of the treatment effect and the prediction of PA progression after PR discharge.

## Methods/design

### Study design

The study will be conducted using a randomized controlled intervention design with five measurement time points (t0–t4; see Fig. 1).

**Fig. 1 Fig1:**
[figure not shown]
Study flow chart of subjects

### Study population

The study will take place within the German rehabilitation system which typically provides an inpatient rehabilitation in a disease-specific rehabilitation clinic for a duration of 3 weeks. Eligible are patients with COPD in all 2011 GOLD classifications A–D [18] and stages 1–4 who are enrolled for PR with the rehabilitation clinic Bad Reichenhall, the largest PR clinic in Germany. Recruitment starts in June 2016 and is likely to be finished in September 2017.

Table 1 provides an overview of all inclusion and exclusion criteria. The study nurse verifies inclusion criteria based on the written information available from the general practitioner who filed the application for PR. At the start of PR the admitting physician confirms the inclusion and exclusion criteria during the initial examination.

**Table 1 Tab1:** Study inclusion and exclusion criteria

Inclusion criteria (*ICD-10*)	Main diagnosis for the pulmonary rehabilitation: physician-confirmed diagnosis of chronic obstructive pulmonary disease (COPD) (International classification code: J44.- at all 2011 GOLD classifications A–D). The diagnosis has to be confirmed in each case by lung function (FEV_1_/VC < 0.7 after bronchospasmolysis) and a respiratory specialist at admission to the pulmonary rehabilitation clinic Age ≥ 18 years
Exclusion criteria	Severe comorbidities, which will affect the results of the outcome parameters much more than pulmonary rehabilitation; for example, cancer or severe cardiac or neurological comorbidities
	Considerable reduction of sight and hearing
	Severe psychiatric condition as a secondary diagnosis
	Lack of ability to speak German

*ICD-10* International Classification of Diseases, version 10

### Study flow and recruitment procedures

This study consists of two phases (see Fig. 2). Phase I consists of the measurement point t0 2 weeks before the start of inpatient PR. Subjects in study phase I are asked to participate in phase II (t1–t4) upon arrival for PR.

**Fig. 2 Fig2:**

Standard Protocol Items: Recommendation for Interventional Trials (SPIRIT) figure [37–57]

Six weeks before the start of PR, eligible subjects will be contacted in writing by the PR clinic study nurse. The letter contains detailed information about the process of study phase I. Furthermore, patients are asked for their consent to be contacted via telephone. Persons who agree will be called by the study nurse, provided with further information about the study and asked to participate in study phase I. Participants return written informed consent via a prepaid envelope. This form provides the necessary consent for participation in the t0 measurement. The PA monitor will then be shipped out from the Erlangen study center. Enclosed along with the PA monitor, participants receive precise, illustrated instructions for wearing the PA monitor. Additional telephone support will be available from the Erlangen study center for all questions regarding study phase I, including any accelerometer issues.

Study phase II starts with the beginning of inpatient PR. During initial PR admission assessment subjects of study phase I will be informed about the course of the study phase II (t1–t4). A second signed informed consent is required for participation in phase II of the study. Subjects will then be randomized into two study arms, either the control group (CG) or the intervention group (IG). All subjects will first undergo an initial assessment of PA-related health competence (t1). Before the start of the study interventions (see the “Interventions” section below) in week 2 of the inpatient PR, CG and IG will each receive a short introductory session explaining the use of PA monitors. At the end of the inpatient PR, the assessment battery from t1 will be repeated (t2).

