### Randomization

The randomization of subjects in study phase II is carried out by a study nurse after initial physical examination using an externally provided randomization list from the Friedrich-Alexander-Universität Erlangen-Nürnberg. Randomization is stratified based on the four prognostic dichotomous variables sex (male vs. female), progression of COPD (GOLD stages 1–2 vs. stages 3–4), age (<60 years vs. ≥ 60 years), and type of rehabilitation (PR in patients with stable COPD vs. PR after hospitalization due to subsequent COPD-related airway obstruction). The randomization list is created in blocks with six subjects per block. The study nurse is aware of the allocation in the different strata. The randomization scheme was generated by using the website Randomization.com.

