### Outcome assessment

#### Primary outcome measures

The primary outcome is objectively measured PA at 6 weeks (t3) and 6 months (t4) after PR. Baseline measurement of PA is conducted 2 weeks before the inpatient PR begins (T0). PA is measured on seven consecutive days with a three-axial accelerometer PA monitor (Actigraph wGT3X-BT). This activity monitor is the one of the most accurate devices for COPD patients and is explicitly recommended as a valid tool to measure PA in this clinical population [21–23].

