### Data analysis

#### Statistical analysis and evaluation

Regarding the primary objective, a baseline-controlled comparison (covariance) of the post values between the initial assigned control and the intervention treatment group (intention-to-treat analysis) at the time points t3 and t4 will be provided for statistical analysis.

For the secondary objective a cluster-based analysis method will be used for longitudinal records (e.g., linking of clusters after removal of a residue (LICUR); [25]). In this case the analysis creates separate clusters for each measurement using the comprehensive assessment battery for t1 and t2 and especially using the accelerometer PA data for t0, t3 and t4. The second step of the cluster-based analysis links separately created clusters in a longitudinal way.

A strategy for dealing with missing data will be developed in cooperation with a biostatistician. If adequate and realistic, missing data will be substituted by multiple imputation.

The processing of PA monitoring data as the primary outcome will be conducted as follows: the PA monitor will be worn for seven consecutive days with a minimum of four valid days inclusive of a weekend day [26–28]. A day is considered valid if subjects wear the device for ten or more waking hours [26–28], where non-wear time is set at 60 min of zero counts of which up to 2 min may be within the 0–100 count range [28, 29]. Current research points towards avoiding the use of direct monitor outputs such as energy expenditure estimations due to issues with reliability [21, 30]. Consensus points towards the use of both sedentary and moderate to vigorous physical activity (MVPA) cutoff points where sedentary activity is seen as 0 to > 100 counts per min [27, 29, 31, 32] and MVPA as > 1952 counts per min [29]. While the use of the LFE filter to calculate steps is not recommended, it may be applicable during data analysis of cutoff points for older adults [33, 34]. Future work on defining cutoff points in clinical populations will be considered.

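### The trial stratifies on rehabilitation after hospitalization, but the article does not show how those patients pass through the six-week postal entry path or when their t0 falls relative to the hospital stay

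*Protocol article*

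**What the plan says.** The Randomization section of the protocol article states that "Randomization is stratified based on the four prognostic dichotomous variables". One of the four is "type of rehabilitation (PR in patients with stable COPD vs. PR after hospitalization due to subsequent COPD-related airway obstruction".

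Entry is described step by step, with a single route:

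- Study population: "The study nurse verifies inclusion criteria based on the written information available from the general practitioner who filed the application for PR".
- Study flow and recruitment procedures (text after Fig. 2): "Six weeks before the start of PR, eligible subjects will be contacted in writing by the PR clinic study nurse". Agreement to be telephoned, the call, consent returned by post and shipment of the monitor come next.
- Study flow and recruitment procedures: "Phase I consists of the measurement point t0 2 weeks before the start of inpatient PR". The Dropout criteria section places this recording at home.
- Study flow and recruitment procedures: "Subjects in study phase I are asked to participate in phase II (t1–t4) upon arrival for PR". Randomization follows at that stage, and no other way into phase II is described.

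The Follow-up phase section makes sending the monitor at t3 and t4 depend on the participant's current health. No such check is stated for t0.

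Under Statistical analysis and evaluation, the primary analysis is a baseline-adjusted covariance comparison of the arms at t3 and t4. The secondary analysis forms clusters, "especially using the accelerometer PA data for t0, t3 and t4", and links them over time. Neither distinguishes patients by type of rehabilitation.

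**The concern.** Setting the post-hospital level against stable COPD suggests patients not long past an acute episode. The entry path suits rehabilitation that is booked well ahead. The article does not explain how the two fit together.

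Two consequences are possible. If few post-hospital patients can follow the path, one level of a stratification factor is nearly empty, and the trial describes a narrower population than the stratification implies. If they do enter soon after a hospital stay, their t0 may reflect illness rather than usual activity. A rise from t0 to t3 would then be partly recovery. That matters most for the clusters, because the Discussion says they will identify patients who struggle to become active whether or not the intervention works. Randomization does not protect that use. In the primary ANCOVA the cost would be precision only.

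**Working it through.** **1. The plan's own figures.** With d = 0.3, f = d/2 = 0.15. The ANCOVA F test with one covariate, two-sided 5%, has noncentrality f²N. At N = 351 this is 0.0225 × 351 = 7.90 and power is 0.8003; at N = 350 power is 0.7991. So 351 reproduces. With 30% dropout, 351/0.70 = 501.4, rounded up to 502. Apart from one degree of freedom, the calculation takes no credit for the covariate, so a poorer t0 does not change either figure.

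**2. Timeline.** Let D be the days from discharge to the start of rehabilitation. The documents do not give D. The letter goes out at about day −42 and t0 is at about day −14.

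| D (assumed) | Letter | t0 |
|---|---|---|
| under about 14 | before discharge | before or during the stay |
| about 14 to 42 | before discharge | 0 to 4 weeks after discharge |
| over 42 | after discharge | more than 4 weeks after discharge |

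In the first two rows a patient can enter only if rehabilitation was already scheduled before or during the stay. In the third row the stated path works unchanged. If nobody in this group could enter, 8 of the 2⁴ = 16 strata would be empty.

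**3. ANCOVA precision.** All inputs here are assumptions: post-hospital share s = 5, 10 or 20%; t0 lowered by δ = 0.5 or 1.0 SD and fully recovered by t3; t0–t3 correlation 0.7 in stable patients and r = 0.3 or 0.7 in post-hospital patients; unit variance within each type.

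Let c = 0.7(1 − s) + r·s and V = 1 + s(1 − s)δ². Residual variances are:

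- t0 only: A = 1 − c²/V
- t0 + type: B = 1 − c²
- t0 × type: C = 1 − 0.49(1 − s) − r²s

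| s | δ | r | A | B | C | A/B | B/C |
|---|---|---|---|---|---|---|---|
| 5% | 0.5 | 0.3 | 0.543 | 0.538 | 0.530 | 1.010 | 1.014 |
| 10% | 1.0 | 0.7 | 0.550 | 0.510 | 0.510 | 1.079 | 1.000 |
| 20% | 1.0 | 0.3 | 0.669 | 0.616 | 0.590 | 1.086 | 1.043 |
| 20% | 1.0 | 0.7 | 0.578 | 0.510 | 0.510 | 1.132 | 1.000 |

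Over all twelve combinations A/B runs from 1.010 to 1.132. Leaving type out therefore makes residual variance about 1–13% higher. Put the other way, adding type lowers it by 1–12%, since 1 − 1/1.132 = 0.117. Letting the t0 slope differ by type gains a further 0–4%.

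**4. Clusters, illustration only.** Under the same assumptions, patients were sorted into thirds separately at t0 and t3, by simulation with 2 million patients per scenario. From recovery alone, 34–52% of post-hospital patients move up a group, against 15–20% of stable patients. At a 10% share they make up 17–24% of all who move up, and at 20% they make up 32–45%. Thirds of one variable stand in for the cluster method and are not the same thing.

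**The case against.** The strongest reply is that nothing states the hospitalization is recent. A reader might infer that post-hospital patients either cannot enter or always have a t0 taken around their stay. The documents do not support that: D is not given, and with D above about 42 days the path works as written. This part of the objection stands, and the point is limited accordingly.

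A reader might also infer that the treatment comparison is biased. It is not. t0 precedes randomization and rehabilitation type is a stratification factor, so an unusual t0 is balanced between arms in expectation. An empty stratum does no harm to allocation either.

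On the clusters, the article names its method only as an example and nowhere counts a t0-to-t3 rise as success. It also calls rehabilitation type prognostic, so clusters that partly reflect hospitalization could be a legitimate result. That is a fair answer to any demand for separate clustering. At shares of 5–20%, 351 complete cases would give only about 18 to 70 post-hospital patients (351 × 0.05 and 351 × 0.20). It does not answer the narrower request that cluster membership be shown by type.

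Finally, a condensed article may leave a special entry route to the full protocol, and covariates beyond baseline are commonly left to the analysis plan. Both are true. But this article sets out the entry sequence in detail and also names the stratum, and the two do not explain each other. Adding type to the model is offered as a cheap improvement; its absence from the article is not called an error.

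**Conclusion.** The point holds in limited form. As described, the entry path and the stratification factor are not reconciled, and the article does not say when t0 falls relative to the hospital stay. Whether this has any practical effect depends on the hospital-to-rehabilitation interval and the post-hospital share, neither of which is given.

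If the interval is short, the possible costs are a modest loss of ANCOVA precision (the 1–13% rests wholly on the assumed share, t0 shift, recovery and correlations), a t0 that is hard to interpret in the linked clusters, and a narrower population than the stratification implies. If the interval exceeds about six weeks, entry proceeds normally and little remains beyond a clarification. In either case the randomized comparison is unbiased and 351 and 502 stand.

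**What to change.** 1. Reconcile the Study flow and recruitment procedures section with the Randomization section. State how patients in the post-hospital stratum enter, the interval from hospitalization to rehabilitation, and when their t0 is recorded relative to the stay.
2. In the t3 and t4 ANCOVA, add type of rehabilitation as a covariate next to t0. It is already recorded for stratification, and the cost is one degree of freedom.
3. Report the number randomized by type of rehabilitation. If the post-hospital stratum is nearly empty, limit the conclusion to planned rehabilitation in stable COPD.
4. When presenting the linked clusters, show membership by type of rehabilitation, so that recovery after a hospital stay is not read as successful activity change.

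No new visits or measurements are needed; the cost is wording, one model term and one or two table rows. A t0 slope that differs by type, separate clustering by type, and omitting t0 in the post-hospital stratum are optional. The first gains only 0–4%, and the other two cost sample size or data.
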